##### Aim 2: Characterize trajectory classes of BDNF methylation and BDNF protein levels following TBI while controlling for potential demographic, injury, and lifestyle covariates

We will use latent class trajectory analysis (LCTA) (113) of *BDNF* methylation and protein levels separately, with the goal of identifying clusters of children with TBI who follow similar recovery trajectories. Some of the major benefits of LCTA are identification of distinct classes, simplification of complex data, and identification of adverse trajectories for potential intervention targets. Another strength given our heterogeneous sample is that probability of membership in each latent class is identified based on biomarker values over time as well as scores on significant covariates. Covariates to be tested will include age, sex, pubertal status, TBI severity, overall injury severity, BMI, and smoking. We will examine biomarker distributions to determine the need for transformations (114). Model selection will involve the iterative estimation of the number and shape of trajectory classes and identification of the best fitting model utilizing the following verified fit indices: Bayesian information criterion statistic, model estimation convergence, percentage of population in each subgroup (>10%), minimization of the residual variance statistic, and examination of posterior subgroup classification probabilities (115–117). Although the literature on power analyses for LCTA is limited (117), the power to identify the appropriate number of classes is highly dependent on separation of the trajectories (115). We believe our final sample is sufficient for several reasons: (1) we have a strong theoretical basis for our hypothesis of at least two classes and expect the classes to be relatively distinct; (2) we intend to evaluate different forms of the extracted model using verified fit indices (115); and (3) LCTA with covariates has been successfully applied in smaller TBI samples, *n* = 100–138 (75, 118–120).

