Aim 1: Examine differences between TBI and OI in *BDNF* methylation and BDNF protein levels over the recovery period. We hypothesize that *BDNF* methylation will be higher, and BDNF protein levels will be lower, in children with TBI relative to OI at all time points, and that *BDNF* methylation will decrease, and BDNF protein levels will increase, in the TBI group over time but will remain relatively stable in the OI group.Aim 2: Characterize trajectory classes of *BDNF* methylation and BDNF protein levels following TBI while controlling for potential demographic, injury, and lifestyle covariates. We hypothesize the presence of at least two *BDNF* methylation trajectory classes and two BDNF protein level trajectory classes representing varying degrees of recovery from TBI. We will explore age, sex, pubertal status, TBI severity, overall injury severity, body mass index (BMI), and smoking as potential covariates.Aim 3: Test the indirect effect of childhood adversity on neurobehavioral recovery following pediatric TBI, as mediated by *BDNF* methylation and BDNF protein level trajectory classes.

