#### Statistical Methods and Power

##### Aim 1: Examine differences between TBI and OI in BDNF methylation and BDNF protein levels over the recovery period

Unadjusted *BDNF* methylation and protein levels will be compared between TBI and OI groups using mixed effects analysis of variance (ANOVA; time as within effect; group as between effect). Mixed effects ANOVA allows for the modeling of effects on continuous outcomes (BDNF methylation and protein levels), is flexible with missing data, and provides explicit estimation of between group and within group variance. We will use appropriate transformations if normality is violated. We expect a significant group × time interaction and group differences at each time point. Alpha will be set at 0.05, and we will adjust for multiple comparisons using Bonferroni corrections. We expect sufficient power (≥0.8) to detect even a small interaction effect (partial η^2^ = 0.01) assuming correlation of 0.5 between repeated measures (G^*^Power 3.1.9.2).

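### If the Aim 2 class models carry no within-class random effects, the listed selection criteria would almost always find two or more classes at a correlation of 0.5, even where none exist

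*Protocol article*

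**What the plan says.** The aims at the end of the protocol article's Introduction make the number of classes a hypothesis: "We hypothesize the presence of at least two *BDNF* methylation trajectory classes and two BDNF protein level trajectory classes". Under Statistical Methods and Power, Aim 2, the method is given as "We will use latent class trajectory analysis (LCTA) (113) of *BDNF* methylation and protein levels separately", in the TBI group. On choosing the number of classes the article says "Model selection will involve the iterative estimation of the number and shape of trajectory classes". Four of the five criteria for that choice read "Bayesian information criterion statistic, model estimation convergence, percentage of population in each subgroup (>10%), minimization of the residual variance statistic". The fifth looks at how confidently children are assigned to their class, with no cut-off given for the posterior probabilities.

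The section gives no numerical power. Its first argument that the sample suffices is "we have a strong theoretical basis for our hypothesis of at least two classes and expect the classes to be relatively distinct". It names neither a one-class model nor a random-effects comparator, and no result that would count against the hypothesis. It also does not say that the search starts at two classes, or that within-class random effects are left out.

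Aim 3 then uses class membership for methylation and protein as categorical mediators between childhood adversity and outcome. The only within-child correlation in the article is in the Aim 1 power statement, for the same biomarkers and visits: "assuming correlation of 0.5 between repeated measures".

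**The concern.** A class model without random effects treats a child's three measurements as independent once class is known. Its one-class version therefore allows no within-child correlation at all. If children vary smoothly in level, adding classes is the only way such a model can represent that variation. BIC then rewards the split whether or not subgroups exist.

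The other criteria offer no protection. Splitting a bell-shaped distribution of levels gives sizeable classes with respectable posterior probabilities, and residual variance falls as classes are added, so that criterion favours more of them.

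Two things are at stake. A report of two classes would be read as confirming the Aim 2 hypothesis when it could only reflect correlation between visits. The same classes would then enter Aim 3 as the proposed mechanism.

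**Working it through.** **The plan's own figures.** Aim 2 states no power or error rate, so there is nothing to reproduce there. As a check on the borrowed correlation, the Aim 1 power was recomputed with G*Power's default convention for a within-between interaction: f² = 0.01/0.99 = 0.0101, λ = f²·N·m/(1−ρ), m = 3, ρ = 0.5.
- N = 225: λ = 0.0101 × 225 × 3/0.5 = 13.6, power 0.92.
- N = 300: λ = 18.2, power 0.975.

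Both agree with the stated power of at least 0.8, so 0.5 is a working input of the plan.

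**Inputs for Aim 2**
- Three visits (Introduction, study design).
- 200 TBI children enrolled, 150 expected at follow-up (Data Reduction, Missing Data, and Attrition).
- ρ = 0.5 from Aim 1; the range 0 to 0.7 was also run.
- Class share above 10% (Aim 2).
- Assumption: no within-class random effects.
- Assumption: a posterior-probability cut-off of 0.70 in one variant.

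**Why the split occurs.** With equal correlation ρ over three visits, det R = (1−ρ)²(1+2ρ). Ignoring the correlation costs about n × (−ln det R) in −2 log-likelihood. With linear class means, a K-class model without random effects has 2K + (K−1) + 1 = 3K parameters. A second class therefore costs 3·ln(n) in BIC, which is 3 × 5.01 = 15.0 at n = 150.

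| ρ | det R | 150 × (−ln det R) | BIC cost of a second class |
|---|---|---|---|
| 0.1 | 0.972 | 4.3 | 15.0 |
| 0.2 | 0.896 | 16.5 | 15.0 |
| 0.3 | 0.784 | 36.5 | 15.0 |
| 0.5 | 0.500 | 104.0 | 15.0 |

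A two-class model need not recover exactly this amount, so the table is only a guide. It puts the turning point near ρ = 0.2.

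**Simulation.** Data came from one normal population with a common linear decline, a random intercept giving correlation ρ, and complete data. There were 200 data sets per cell for ρ below 0.5 and 100 otherwise. Models with one to three classes and independent residuals were chosen by BIC, subject to every class exceeding 10%. Share of data sets with two or more classes:

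| ρ | n = 150 | n = 200 |
|---|---|---|
| 0 | 0% | 0% |
| 0.1 | 5.5% | 7.5% |
| 0.2 | 60% | 78.5% |
| 0.3 | 98% | 100% |
| 0.5 | 99% | 100% |
| 0.7 | 100% | 100% |

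Monte Carlo standard error is at most √(0.6 × 0.4/200) = 3.5 points. At ρ = 0.5:
- The mean number of classes chosen was 2.4 (n = 150) and 2.6 (n = 200).
- The lowest class-specific mean posterior probability averaged 0.87 and 0.86. Requiring 0.70 changed no result.

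A further run with 200 children, 150 of them followed up, gave 100% at ρ = 0.5.

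**With the comparator.** On the same one-population data:
- For ρ of 0.3 or more, the one-class random-intercept model had the better BIC in 99.5–100% of data sets.
- When the class models also carried a random intercept, two classes were chosen in 0–1% at every ρ.

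**Does the comparator hide real classes?** With two true classes and a within-class intercept SD of 0.5 residual SDs, the one-class random-intercept model beat the class models without random effects in 68% of data sets when the classes lay 2 residual SDs apart, and in 0% at 3 SDs apart. Two-class models that carry a random intercept were selected in 98–100% of clearly separated two-class data sets.

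**The case against.** The strongest objection is that the decisive premise is not in the article. Random-effects structure is the kind of detail an article leaves to a fuller analysis plan. The article's iterative search, and its intention to try different model forms, leave room for both a one-class model and random effects. This stands, and it makes the point conditional: with a within-class random intercept the false-split rate is 0–1%. What remains is that the article does set out its selection indices, and none of them can tell subgroups from a continuum.

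A reader might infer that the hypothesis cannot fail, or that any correlated biomarker will be split. The documents do not support that. One class is formally available to BIC, and at correlation 0.1 it is kept in 92.5–94.5% of data sets.

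The 0.5 is a planning value for Aim 1, covering both injury groups. The article describes a sharp acute peak in BDNF protein followed by decline, so the correlation between the acute and later visits could be lower. This also stands, and is why the range is shown.

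The harm to Aim 3 should not be overstated either. False classes would be a coarse cut of real differences between children, not noise. In one run at correlation 0.5, class membership kept about 63–66% of the information on a child's true level that the child's simple mean carried. The study is an exploratory pilot, but Aim 2 still states a hypothesis and the results are meant to guide a larger study.

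Finally, the comparator is imperfect. It can miss moderately separated classes, as shown in the working. With one strongly skewed, untransformed population it won in only 32% of data sets. The article does plan to consider transformations.

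**Conclusion.** The point holds conditionally. If the class models have no within-class random effects, then at a correlation of 0.5 the stated criteria give two or more classes in about 99–100% of data sets drawn from one continuous normal population. The figure is about 60–80% at 0.2 and about 5–8% at 0.1. A two-class result would then be no evidence for the Aim 2 hypothesis, and the Aim 3 mediators could be arbitrary cuts of a continuum.

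This rests on the absence of random effects, which the article neither states nor excludes; on a correlation borrowed from Aim 1; and on normally distributed biomarkers. It is an improvement to the selection rule that should be made, not a demonstration that the planned analysis is invalid.

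**What to change.** After any transformation, include a one-class growth model with a random intercept among the candidates for each biomarker. Fit the multi-class models both with and without a within-class random intercept. Claim distinct classes only if a multi-class model beats the one-class random-intercept model on BIC, with the existing criteria applied as well.

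If none does, report no evidence of distinct classes, and add a sensitivity analysis of Aim 3 that uses each child's continuous level or slope as the mediator.

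The cost is a few extra model fits per biomarker, a sentence or two of text, the added Aim 3 analysis where it applies, and reduced ability to declare classes that are only weakly separated. No new data are needed. Fitting the multi-class models with a random intercept as well limits the loss where classes are as distinct as the article expects.

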##### Aim 3: Test the indirect effect of childhood adversity on neurobehavioral recovery following pediatric TBI, as mediated by BDNF methylation and BDNF protein level trajectory classes

We will conduct path analysis to test the theoretical model shown in Figure 2 within the TBI group. The theoretical model represents the relation among constructs rather than specific measures to allow for fluidity in our approach. For example, we will examine this model for each of the four primary measures of neurobehavioral outcome (NIHTB-CB, BRIEF-2/P, SDQ, Vineland-3). The specific biosamples used for *BDNF* methylation will be informed by preliminary analyses (see *Biomarker Analysis*). Path analysis enables a graphical representation of complex relationships, can explore direct and indirect effects among the variables (e.g., mediation), and infer causal directionality between effects. *BDNF* methylation and protein level trajectory class adjusted for covariates (Aim 2) will be tested as categorical mediators. Neurobehavioral recovery on each outcome will be modeled controlling for premorbid functioning (with the exception of NIHTB-CB). We estimated sample size requirements to adequately power the three single mediator models that would comprise our double-mediator model, as current guidelines on sample size for double mediator models are limited. The power of a single mediator model depends on the effect of the independent variable (IV) on the mediator and the effect of the mediator on the DV, controlling for the IV. Using Cohen's effect size criteria, we expect to have sufficient power (≥0.8) if both effects are at least “halfway” (between small and medium effects) (121). However, we would only need 115 participants if one effect is “halfway” and the other is medium. Thus, our final sample is conservative.

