Data are collected at three time points postinjury. Acute data collection occurs before hospital discharge, and chronic data collection occurs at 6 and 12 months postinjury during outpatient follow-up visits to CHP. Data are collected pertaining to hypothesized predictors of neurobehavioral recovery (e.g., demographics, injury information, child premorbid functioning, childhood adversity, and biomarkers), neurobehavioral outcomes (e.g., neuropsychological test performance, parent-rated neuropsychological, emotional/behavioral, and adaptive functioning), and potential covariates/confounders (e.g., BMI, pubertal status, tobacco/nicotine exposure, bodily injury severity). Recruitment began in July 2017 and will occur for ~6 years, with data collection complete by mid-2023.

DNA methylation patterns are tissue specific and reflect the local environment of each cell type, and examination of brain tissue is not feasible in patients who survive their injuries; therefore, determining which types of biosamples serve as effective proxies for the CNS environment is an important methodological consideration. Moreover, to be useful as a clinical biomarker, markers must be found in readily accessible biosamples, such as blood or saliva. Several previous studies have shown that methylation in peripheral biosamples, including blood and saliva, is strongly correlated with methylation in brain tissue or CSF (46, 76–81) for several target genes, including *BDNF* (46, 77). Methylation measured in peripheral biosamples may be of even greater prognostic value in TBI compared to neuropsychiatric conditions because brain-specific biomarkers may enter blood circulation in TBI not only through disruption to the blood–brain barrier but also through the glymphatic system (82). Finally, a recent review of the “tissue issue” concluded that the limitations of examining epigenetic brain biomarkers in peripheral tissues or biosamples are surmountable and discussed methodological advantages of using peripheral biosamples: serial biosampling, longitudinal study designs and related causal modeling options, large participant sample sizes yielding statistical power to detect modest effects, and translational utility in clinical settings (83).

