In light of these methodological considerations, we collect saliva and blood biosamples at acute and chronic time points in all participants. We also collect acute serial CSF samples in the small subsample of participants with extraventricular drain (EVD) placement to manage intracranial pressure as part of guidelines based standard of care (84).

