### Outcomes

Child neuropsychological function is assessed acutely and at each follow-up visit using the NIHTB-CB (97). The NIHTB-CB is a 30-min battery of standardized neuropsychological tests administered on an iPad. The NIHTB-CB provides norm-referenced scores for the domains of language, episodic memory, processing speed, working memory, and executive function, as well as an overall cognitive function composite score.

Parent-reported child postinjury executive, emotional/ behavioral, and adaptive functioning are measured at follow-up visits using the BRIEF-2/P, SDQ, Vineland-3, and resilience items from the CHIP. Postinjury adversity is measured using the PAT and child resilience by the CHIP.

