### Significance

Successful completion of the proposed aims has the potential to improve patient outcomes by advancing the field of pediatric TBI toward precision rehabilitation medicine. The unexplained heterogeneity in outcomes that plagues the field of TBI suggests a critical need to harness the potential of personal biology in predicting individual patient outcomes and response to interventions. The measurement of *BDNF* methylation and levels from accessible biosamples may serve as an early postinjury biomarker that more accurately predicts neurobehavioral outcomes following pediatric TBI, thereby allowing for earlier identification of children at greatest risk for poor recovery and the early provision of targeted intervention. Further understanding of the role of *BDNF* in recovery from TBI and the preinjury environmental determinants of its expression may bring us closer to being able to translate interventions to humans that have increased *BDNF* expression and improved cognitive outcomes in animal models, namely, environmental enrichment (63, 124) and exercise (125, 126). Finally, no neuroprotective therapies are currently available for TBI (127). Thus, demonstrating a possible role for *BDNF* epigenetics in mediating neurobehavioral outcomes will identify *BDNF* methylation as a possible target for the development of medical therapeutics. Interventions using epigenetic-based therapies have shown promise in experimental models of TBI (128, 129). This work will provide the foundation to develop biologically grounded, personalized approaches to treatment and rehabilitation that may apply across multiple child and adult brain disorders.

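### Aim 3's trajectory-class mediators overlap in time with the outcomes they are meant to explain, so path analysis cannot establish causal direction from them

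*Protocol article*

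**What the plan says.** **Mediator.** Statistical Methods and Power, Aim 3, states that BDNF "methylation and protein level trajectory class adjusted for covariates (Aim 2) will be tested as categorical mediators". Aim 2 says how a class is formed: "probability of membership in each latent class is identified based on biomarker values over time as well as scores on significant covariates".

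**Biomarker timing.** Study Overview: "we collect saliva and blood biosamples at acute and chronic time points in all participants". It defines the later points: "chronic data collection occurs at 6 and 12 months postinjury during outpatient follow-up visits to CHP".

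**Outcome timing.** In the Outcomes section, the parent-reported domains of postinjury "functioning are measured at follow-up visits using the BRIEF-2/P, SDQ, Vineland-3". The NIHTB-CB is given acutely as well as at both follow-up visits. Aim 3 does not name the outcome visit that enters the model.

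**Causal claim.** The same Aim 3 paragraph says that path analysis can "infer causal directionality between effects". Outcomes are adjusted for premorbid functioning, except for the NIHTB-CB. The article describes no lag, no acute-only mediator and no outcome visit after the last biosample.

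**The concern.** A mediator has to come before the outcome it explains. A class that describes the course from injury to 12 months is complete only at 12 months, and no outcome visit follows. Path analysis does not supply the missing order. The analyst draws the arrows, and with variables from the same visit a model with the mediator-outcome arrow reversed can fit equally well.

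The protocol itself points to routes by which recovery could move the later biomarkers. Potential Covariates/Confounds says that BDNF measures vary with BMI, smoking and pubertal status. Strengths and Potential Limitations adds diet, exercise, and alcohol and drug exposure, which are not measured. Several of these can change with how well a child recovers. Adjusting for preinjury functioning does not remove an effect of postinjury state on later samples.

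Aim 3 is the test of the study's primary hypothesis. The risk is that an indirect effect produced by reverse influence is reported as evidence that BDNF transmits the effect of adversity to recovery.

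**Working it through.** **1. Temporal order, from the visit schedule**

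| Outcome taken at | Acute biomarker | 6-month biomarker | 12-month biomarker |
|---|---|---|---|
| 6 months | before | same visit | after |
| 12 months | before | before | same visit |

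Only the acute part precedes both outcome visits. Neither outcome visit follows a complete three-visit class. Aim 2 does not list the visits by name, but a trajectory cannot be formed from the acute visit alone.

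**2. The plan's own figure**

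Aim 3 expects power of at least 0.8 if both paths are halfway between small and medium. Assume Cohen's f² of 0.02 (small) and 0.15 (medium), slope = √f², a continuous mediator and two-sided alpha 0.05. The slopes are then 0.141 and 0.387, and halfway is (0.141 + 0.387)/2 = 0.264. With the 150 TBI follow-up participants, simulated power is 0.78–0.79 by joint significance and 0.84 by bias-corrected bootstrap. With 115 participants (one halfway path, one medium) it is 0.77–0.78 and 0.83. The stated power is reproduced with the bootstrap. The timing point does not depend on it, but n = 150 and a path of about 0.265 are carried forward.

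**3. Class-outcome path with no effect of biomarker on outcome**

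Assumed model: biomarker at visit t = √0.5·U + √0.5·E_t, where U is a person factor, so visits correlate 0.5. The outcome depends only on E at 12 months, or on E at 12 and 6 months. The class is a median split of the three-visit mean, standing in for a two-class solution.

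- Variance of the mean: 0.5 + 0.5/3 = 0.667, SD 0.816.
- Correlation of the mean with the outcome: (sum of the visit correlations)/3/0.816. A median split multiplies this by √(2/π) = 0.798.
- Power: P(Z > 1.96 − r·√147), with √147 = 12.12, ignoring the far tail.

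With 0.3 at 12 months only: 0.3/3/0.816 = 0.122; × 0.798 = 0.098; 0.098 × 12.12 = 1.19; P(Z > 0.77) = 0.22.

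With a further 0.15 at 6 months: 0.45/3/0.816 = 0.184; × 0.798 = 0.147; 0.147 × 12.12 = 1.78; P(Z > 0.18) = 0.43.

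Simulation gives about 22% and 44%. If 0.3 and 0.15 are instead loadings on the visit-specific part only, they correspond to biomarker correlations of 0.21 and 0.11 (× √0.5), and the rates fall to about 14% and 24%. The acute biomarker alone stays near 5%.

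**4. Indirect effect, which is what Aim 3 tests**

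Joint significance needs the adversity-mediator path as well.

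- No adversity-biomarker path: roughly 0.05 × 0.22 = 0.011 and 0.05 × 0.44 = 0.022, so 1–2%.
- Adversity path of 0.265 to the person factor: correlation with the class 0.265 × 0.707/0.816 × 0.798 = 0.183; 0.183 × 12.12 = 2.22; P(Z > −0.26) = 0.60. The products are 0.60 × 0.22 = 0.13 and 0.60 × 0.44 = 0.26. Simulation gives about 15% and 25%.
- On the visit-specific reading, simulation gives about 8% and 14%.

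**5. A second set-up**

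Here the outcome acts directly on the same-visit biomarker with slope 0, 0.14, 0.265 or 0.39, classes come from a two-class mixture, and the 12-month outcome is adjusted for the premorbid score.

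| Reverse slope | False mediation, adversity path 0.265 | False mediation, no adversity path |
|---|---|---|
| 0 | 3% | 0.4% |
| 0.14 | 10% | 0.6% |
| 0.265 | 27% | 3.5% |
| 0.39 | 52% | 11% |

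With the acute biomarker alone as mediator, the rate is about 4% in every row of the middle column and 0.5% or less in the last.

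**The case against.** The study is presented as an exploratory pilot, its conclusions are hedged, and the causal clause is one phrase in a general description of path analysis. That stands and lowers the severity, but it does not make the phrase correct.

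The hypothesis concerns biomarkers in response to injury and across recovery. An acute sample, taken within a week of injury and near the reported BDNF peak, does not test that, and two visits cannot show a nonlinear course. This also stands: replacing the three-visit class would change the aim's question.

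BMI is collected at every visit and is a candidate covariate, so weight change is partly covered. Reverse influence by other routes is not.

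A reader might infer three stronger points that the documents do not support:

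- **That Aim 3 would report false mediation in 22% or 44% of studies.** Those rates belong to the class-outcome path alone. The indirect effect also needs an adversity-biomarker path, and without one the rate in that set-up is 1–2%.
- **That the order of the two mediators is undefined.** The Introduction gives a theoretical order, with methylation regulating BDNF synthesis. Figure 2, which sets out the Aim 3 paths, is not shown in the text available, so its ordering cannot be judged. What is lacking is separation in time.
- **That the Significance section contradicts Aim 3.** Its statement that BDNF methylation and levels "may serve as an early postinjury biomarker that more accurately predicts neurobehavioral outcomes" concerns measurements, not trajectory classes, and acute measurements are collected.

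**Conclusion.** The point holds. The class mediators share the 6- and 12-month visits with the outcomes, no outcome follows the full mediator, and the claim to infer direction is wrong as written. The acute part of the class does precede the follow-up outcomes, and adversity is first measured acutely, so the fault is confined to the mediator-outcome step.

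The size depends on effects that the documents do not give. In the main illustration, the false indirect effect ranges from about 1–2% with no adversity-biomarker path to 15–25% with a 0.265 path (8–14% on the visit-specific reading). The second set-up shows that it can be larger if recovery acts strongly on the biomarker. These figures show that the mechanism can matter; they do not predict this study's error rate. The plan should be corrected, but the weakness is not disqualifying in an exploratory pilot.

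**What to change.** 1. In Statistical Methods and Power, Aim 3, delete the clause on causal directionality, or replace it with a statement that the model assumes the direction of each path.
2. Keep the three-visit class model, which answers the question about the recovery period, and report its mediator-outcome path as an association.
3. Add a prespecified, temporally ordered analysis: adversity → acute (or acute and 6-month) methylation and protein → 12-month outcome, adjusted for the premorbid score where there is one. Claim mediation only if this analysis supports it. The acute version is the cleaner of the two, because a 6-month sample can still reflect 6-month status that persists to 12 months.

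**Cost.** No new data or visits are needed. The price is one more analysis, a mediator resting on one or two samples instead of three, and a more cautious conclusion.
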